## Abstract

**Introduction:**

In people with Parkinson’s (PwP) impaired mobility is associated with an increased falls risk. To improve mobility, dopaminergic medication is typically prescribed, but complex medication regimens result in suboptimal adherence. Exploring medication adherence and its impact on mobility in PwP will provide essential insights to optimise medication regimens and improve mobility. However, this is typically assessed in controlled environments, during one-off clinical assessments. Digital health technology (DHT) presents a means to overcome this, by continuously and remotely monitoring mobility and medication adherence. This study aims to use a novel DHT system (DHTS) (comprising of a smartphone, smartwatch and inertial measurement unit (IMU)) to assess self-reported medication adherence, and its impact on digital mobility outcomes (DMOs) in PwP.

**Methods and analysis:**

This single-centre, UK-based study, will recruit 55 participants with Parkinson’s. Participants will complete a range of clinical, and physical assessments. Participants will interact with a DHTS over 7 days, to assess self-reported medication adherence, and monitor mobility and contextual factors in the real world. Participants will complete a motor complications diary (ON-OFF-Dyskinesia) throughout the monitoring period and, at the end, a questionnaire and series of open-text questions to evaluate DHTS usability. Feasibility of the DHTS and the motor complications diary will be assessed. Validated algorithms will quantify DMOs from IMU walking activity. Time series modelling and deep learning techniques will model and predict DMO response to medication and effects of contextual factors. This study will provide essential insights into medication adherence and its effect on real-world mobility in PwP, providing insights to optimise medication regimens.

**Ethics and dissemination:**

Ethical approval was granted by London—142 Westminster Research Ethics Committee (REC: 21/PR/0469), protocol V.2.4. Results will be published in peer-reviewed journals. All participants will provide written, informed consent.

**Trial registration number:**

ISRCTN13156149.

STRENGTHS AND LIMITATIONS OF THIS STUDYThis protocol has been developed by a multidisciplinary team of experienced clinicians, researchers and data analysts.This study will monitor mobility and assess self-reported medication adherence in the real world, enhancing the ecological validity of results.If efficacious, this protocol may be implemented in clinical settings to optimise medication regimens and enhance the quality of life for people with Parkinson’s disease.Participants will only be required to attend a single clinic-based assessment, with the remainder of the study conducted in their home or community.This study will include participants with mild to moderate disease severity, therefore, our conclusions may not reflect the experience of those with more advanced Parkinson’s disease.

## Introduction

Mobility, defined as the ability to freely move about one’s environment, is a key contributor to overall health and maintaining independence.^1 2^ People with Parkinson’s (PwP) experience a loss of mobility due to the cardinal motor symptoms of bradykinesia, rigidity, tremor and postural instability.^3^ This loss of mobility is associated with an increased risk of falls and reduced independence; therefore, mitigating mobility loss in PwP is of primary importance.^4^

In PwP, dopaminergic medications (eg, levodopa) are commonly prescribed to alleviate motor symptoms and improve mobility.^3^ Medication is often prescribed in multiple doses throughout the day, with adherence to prescribed dosage and timing essential to alleviate motor symptoms and avoid fluctuations, especially as the disease progresses. Complex medication regimens result in suboptimal adherence, poor medication responses and reduced quality of life.^5–7^ Modification to regimens often follows patient-reported outcomes and short, infrequent clinical appointments, with clinicians observing patients during specific stages in their regimen (eg, ON/OFF periods). Consequently, clinicians often lack adequate insight into patient’s medication habits and daily fluctuations in motor symptoms to appropriately adapt regimens. Understanding medication adherence in PwP and its effect on their everyday mobility and motor symptoms would ensure more effective and personalised patient management, allowing clinicians to optimise dose and frequency of dopaminergic medication.

At present, research exploring medication and mobility in PwP is typically conducted in controlled lab-based or clinical environments, in specific ON/OFF medication states.^8–16^ Although some studies have been performed in the real world (ie, daily living, outside clinical or laboratory settings),^17 18^ a more granular picture is required. Digital health technology (DHT) presents the tools to explore this, by allowing for the continuous assessment of medication adherence and mobility (digital mobility outcomes, DMOs) in the real world.^5 19–22^ A variety of DMOs can be used to assess mobility; and of primary interest is walking speed.^23^ Walking speed reflects overall health in PwP and declines overtime, with slow walking speed associated with adverse clinical events such as an increased risk of falls;^4^ therefore, assessing this DMO can provide insights into medication related changes in overall mobility and health. The COVID-19 pandemic has also highlighted the fragility of clinic-based care for PwP and reinforced the necessity to use DHT to improve current practice.^24^

There are a variety of DHTs which can monitor individuals during their day-to-day lives. For example, the Personal KineticGraph (Global kinetics Corp, Australia), a wrist-worn device, can send medication reminders and continuously monitor motor symptoms such as bradykinesia, tremor and dyskinesia.^25 26^ However, technology such as this cannot monitor the specific medication ingested or quantify gait characteristics. Future research should, therefore, focus on developing a DHT system (DHTS), which can comprehensively and remotely assess medication adherence and monitor mobility. Data collected using this system would allow for the creation of data driven models to investigate variations in mobility following medication intake, thus providing greater insights for optimised medication regimens in PwP.

This study aims to collect real-world data using a novel DHTS (smartphone, smartwatch and inertial measurement unit, IMU) to assess self-reported medication adherence, quantify DMOs and model and predict their response to medication. Within this study, specific objectives include: (1) clinically characterise our participants with Parkinson’s (eg, Hoehn and Yahr stage, disease duration); (2) collect real-world data with a connected DHTS in PwP; (3) assess real-world, self-reported medication adherence in PwP by recording medication intakes (smartwatch reminders, time of logged intakes and acknowledged medication intake events); (4) quantify real-world DMOs (eg, walking speed) and (5) model and predict response of DMOs to Parkinson’s medication.

## Methods and analysis

The Standard Protocol Items: Recommendations for Interventional Trials (SPIRIT) reporting guidelines have been followed within this manuscript^27^ (online supplemental material 1). This protocol represents protocol V2.4, April 2022.

10.1136/bmjopen-2023-073388.supp1Supplementary data

### Study design and setting

This cross-sectional, observational study will recruit 55 participants with Parkinson’s disease (IRAS Number: 295771). It will be conducted at the Clinical Ageing Research Unit, [name], with a remote home and community-based component. The study is cofunded by the Medical Research Council (MRC) Newcastle University, the UK Research Innovation, Engineering and Physical Sciences Research Council (UKRI ESPRC) and the National Institute of Health Research (NIHR). This study is a substudy of the ‘Mobilise-D—Clinical Validation Study’ (IRAS Number: 289 543 and REC reference: 20/PR/0792), a longitudinal study, which aims to validate a novel digital method for remote monitoring of mobility.^28^

### Study procedure and flow

#### Recruitment and screening

In this single-centre study, participants will be identified and recruited between June 2021 and June 2024 through the ‘Mobilise-D—Clinical Validation Study’ Newcastle upon Tyne site, and independently through local movement disorder clinics and research registries. As recruitment commenced in the height of the COVID-19 pandemic—that is, when individuals were less mobile, less likely to partake in research, and there was insecurity surrounding future lockdowns—an extended recruitment period was afforded to this study. This was to ensure our sample size was achieved and results were representative. Interested and potentially eligible participants will attend a screening appointment during which informed consent will be obtained, and eligibility confirmed. Informed consent will be taken by the chief investigator or a delegated member of the research team. At the beginning of the screening appointment and prior to further discussion, the individual obtaining consent will confirm that the potential participant has read the participant information sheet (PIS), and will answer any questions. On agreement to participate in the study, the participant will sign and date the informed consent form and the researcher will witness this, and sign and date the same form (online supplemental materials 2 and 3). The process will then be recorded in the participants’ medical records, with the original filed on site and a copy given to the participant. Those recruited through the Mobilise-D study will attend a screening appointment within a Mobilise-D visit and those recruited independently will attend a separate screening appointment. A full outline of the recruitment procedure is detailed in figure 1. All participants will be reimbursed for travel expenses.

10.1136/bmjopen-2023-073388.supp2Supplementary data

10.1136/bmjopen-2023-073388.supp3Supplementary data

**Figure 1 F1:**
[figure not shown]
Flow chart of recruitment and screening procedure. DHTS, digital health technology system; PD, Parkinson’s disease.

Due to the paucity of research exploring the influence of medication on real-world mobility in PwP using a DHTS, there was insufficient data to inform a reliable power calculation before the study commenced. Therefore, a convenience sample size of 55 was defined according to COnsensus-based Standards for selection of health Measurement Instruments guidelines,^29^ with the plan to assess this once 50% of data was collected. The sample size was evaluated using data collected in 30 participants, with GPower V.3.1, assuming an effect size of 0.44 for a change in mobility (gait speed, shown to be improved by levodopa in lab studies)^16^ related to off versus on state (repeated paired t-test, alpha of 0.05 and beta (power) of 0.95). This highlighted that our sample size of 55 participants was appropriate.

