#### Participants and eligibility criteria

Participants with mild to moderate disease severity will be recruited (Hoehn and Yahr stages I–III). The eligibility criteria (inclusion and exclusion) are in agreement with the Mobilise-D study and are detailed in table 1. Potential participants will not be recruited if they have received and/or are due to receive a medication review within 4 weeks of the study assessment. Individuals with more advanced Parkinson’s (Hoehn and Yahr stages IV and V) often possess a decreased ability to efficiently perform activities of daily living and experience cognitive impairment. These factors may induce difficulties to monitor mobility and alter the participant’s ability to interact with the DHTS, respectively. Consequently, only individuals at Hoehn and Yahr stagess I–III will be recruited in this study.

**Table 1 T1:** Inclusion and exclusion criteria

Inclusion criteria	Exclusion criteria
Adults aged 18 or over	Occurrence of any of the following within 3 months prior to informed consent: myocardial infarction, hospitalisation for unstable angina, stroke, coronary artery bypass graft, percutaneous coronary intervention, implantation of a cardiac resynchronisation therapy device, active treatment for cancer or other malignant disease, uncontrolled congestive heart disease (New York Heart Association (NYHA) class >3), acute psychosis, major psychiatric disorders or continued substance abuse
Ability to consent and comply with study specific procedures	History consistent with Dementia with Lewy bodies, atypical parkinsonian syndromes (including multiple system atrophy or progressive supranuclear palsy, diagnosed according to accepted criteria)
Able to read and write in English	Repeated strokes or stepwise progression of symptoms, leading to a diagnosis of ‘vascular parkinsonism’
Patients with the clinical diagnosis of Parkinson’s according to the Movement Disorder Society criteria^47^	Drug-induced Parkinsonism
Hoehn and Yahr stages I–III^48^	
On stable Parkinson’s medication doses (taking the same medication for 4 weeks or more)	
Able to walk 4 metres independently with or without walking aids	
Willingness to wear and interact with a smartwatch and IMU, and carry a smartphone	

IMU, inertial measurement unit.

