### Statistical analysis

Participants’ descriptive, clinical and Parkinson’s specific characteristics, as well as data derived from the DHTS and motor complications diary data, will be analysed using descriptive statistics, including percentage and frequency, mean and SD or median and IQR, as appropriate.

Functional data analysis and deep learning techniques^42^ will be used to model and predict DMO response to medication, and potential effects of contextual factors. DMO trends will be analysed between medication intake times and wearing-off effects will be evaluated via a customised scoring system. This scoring system will identify the wear off periods, grouping them relative to the strength of their effect. Non-linear time series analysis will assess changes in DMOs between medication intakes.^39 43^ Data collected using motor complications diaries will be used to optimise time series modelling of DMOs.

Should the data collected require an adjusted methodology, proposed statistical methods will be amended following completion of data collection.

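### The power figure that confirms 55 participants is for a paired OFF-versus-ON gait speed test that the statistical analysis section does not list, and 55 pairs give about 95% power only if the test is one-sided

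*Protocol article*

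**What the plan says.** The sample size paragraph (Recruitment and screening, after Figure 1) says that data were too sparse for a reliable power calculation at the outset, so 55 was chosen as a convenience sample following a measurement-instrument guideline. After 30 participants the number was checked in GPower, assuming "an effect size of 0.44 for a change in mobility (gait speed, shown to be improved by levodopa in lab studies"), "related to off versus on state (repeated paired t-test, alpha of 0.05 and beta (power) of 0.95"). The paragraph concludes that 55 is appropriate. It does not say how OFF and ON are defined for this test, whether the test is one- or two-sided, or whether any of the 55 are expected to lack a pair.

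The Statistical analysis section plans descriptive statistics, then functional data analysis and deep learning, which "will be used to model and predict DMO response to medication, and potential effects of contextual factors". It adds a customised wearing-off score and non-linear time series analysis of changes between intakes. Diary data are summarised and used to tune the time series models. Methods may be changed once data collection is complete.

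Three other places bear on the number of pairs:
- Table 1 admits Hoehn and Yahr stages I–III on stable medication ("taking the same medication for 4 weeks or more") and does not require OFF time or motor fluctuations.
- The diary section gives the only definition of OFF, which is the participant's own report.
- The Data analysis section keeps only participants with 3 or more days of mobility data.

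**The concern.** Walking speed is one of the two primary outcomes in the section on the seven-day monitoring period. The article gives one power figure for it, and that figure describes a test the analysis section does not plan. None of the methods listed there has a size justification of its own. A reader told that 55 is appropriate at 95% power will attach that assurance to whatever walking speed result is reported, although it applies to none of the listed analyses. Because methods may be revised after data collection, no stated contrast limits how the medication effect on walking speed is finally tested.

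The figure also assumes that every participant supplies a pair. A paired test uses only people with walking recorded in both states. The eligibility criteria and the 3-day rule both leave room for fewer than 55, and no allowance is stated.

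**Working it through.** **Inputs.** From the sample size paragraph: effect size 0.44, alpha 0.05, power 0.95 (printed as "beta (power) of 0.95" and read as power), n = 55, paired t-test. Three readings are assumed because the article does not settle them:
- 0.44 is the mean paired difference divided by the SD of the differences.
- Sidedness is open, so both versions are computed.
- Gait speed in the power paragraph is the primary walking speed outcome (the article also lists gait speed as an example of a secondary micro outcome).

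**Formula.** With n pairs, df = n − 1 and noncentrality = 0.44 × √n. Power is the probability that a noncentral t variable exceeds the critical value t(1 − 0.05; df) one-sided, or lies outside ± t(1 − 0.025; df) two-sided.

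**Step 1: reproduce the stated figure.** For n = 55, noncentrality = 0.44 × 7.416 = 3.263 and df = 54.
- One-sided, critical value 1.674: power 94.3%. The smallest n for 95% is 58. Normal approximation: ((1.645 + 1.645)/0.44)² = 55.9, so 56.
- Two-sided, critical value 2.005: power 89.3%. The smallest n for 95% is 70. Normal approximation: ((1.960 + 1.645)/0.44)² = 67.1, so 68.

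The stated 95% at 55 is therefore matched approximately by a one-sided test with all 55 paired, and not by a two-sided test.

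**Step 2: allow for missing pairs.** The share with usable walking in both states is not in the article. The shares below are assumptions chosen to show a range. Each loss is measured against the 55-pair baseline of the same sidedness.

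| Assumed share | Pairs | Noncentrality | One-sided power (loss from 94.3%) | Two-sided power (loss from 89.3%) |
|---|---|---|---|---|
| 100% | 55 | 3.263 | 94.3% | 89.3% |
| 80% | 44 | 2.919 | 89.0% (5.3 points) | 81.4% (7.9 points) |
| 60% | 33 | 2.528 | 79.6% (14.7 points) | 68.8% (20.5 points) |
| 40% | 22 | 2.064 | 63.7% (30.6 points) | 50.4% (38.9 points) |

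**Step 3: compare the powered test with the planned analyses.** The sample size paragraph powers a two-state, within-person mean difference. The Statistical analysis section models trajectories between intakes, scores wearing-off and predicts response. It uses diary ON/OFF time as a descriptive outcome and to tune models, not as the two arms of a comparison. Power for the functional, deep-learning or time series analyses cannot be computed from what the article gives.

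**The case against.** The strongest reply is that 55 never rested on this test. It was a convenience sample in a cross-sectional observational study whose objectives are to describe, quantify and model, and the t-test was a later check. Sizing a complex longitudinal model by a simpler paired contrast is common, and a separate analysis plan may name the contrast. The first part stands: it would be wrong to say that the t-test produced the 55. But the article uses the check to call 55 appropriate, and its own analysis section does not connect that check to anything planned. This is a mismatch between two printed sections, not a complaint about omitted detail.

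Other stronger readings are tempting but not supported:
- **Participants without OFF time certainly drop out.** This holds only if OFF means diary OFF. The power paragraph leaves OFF undefined, and the Data analysis section links intake timestamps to IMU data. If the states were windows around a dose, people with no diary OFF could still form a pair. The article does not say so, hence may be below 55, not is below 55.
- **0.44 is a laboratory value.** The mention of lab studies may only explain the choice of gait speed, since the check is said to use data from 30 participants. The source is unclear, so there is no basis here for asserting a smaller real-world effect.
- **The Introduction disowns laboratory ON/OFF states.** It says only that such research "is typically conducted in controlled lab-based or clinical environments, in specific ON/OFF medication states" and that finer detail is needed.
- **The whole gap from 95% to the two-sided figures is lost pairs.** About 6 points of it (95 − 89.3 = 5.7) is present with all 55 paired on a two-sided test.

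**Conclusion.** The point holds as a mismatch that should be corrected. The one power figure for a primary outcome belongs to no listed analysis. On its own terms it is 94.3% one-sided and 89.3% two-sided with 55 complete pairs, so the stated 95% is met only approximately, and only under an unstated one-sided test with no loss.

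The mismatch and the unstated sidedness do not depend on how OFF is defined. The recomputed powers rest on reading 0.44 as the standardised paired difference. The further loss from missing pairs depends on the definition of OFF and on a share the article does not give, so it is a range and not an estimate.

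A reader might infer that the study is underpowered or that its modelling should be demoted to exploratory. The article supports neither: the actual number of pairs is unknown, and the modelling serves objective 5 directly.

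**What to change.** 1. Add one prespecified walking speed contrast: the within-person OFF-minus-ON difference. Define OFF and ON (diary period or dose-timing window), and analyse by a paired test or a mixed model with participant random effects.
2. State whether the test is one- or two-sided and where 0.44 comes from, including which standardised effect it is.
3. From the first 30 participants, report the share with walking recorded in both states under that definition who also meet the 3-day rule. Restate power for that share of 55, for this same contrast, so that the power figure and the analysis correspond.
4. Keep the functional, time series and deep-learning models for objective 5, with a sentence saying that the power figure does not apply to them.

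The cost is some wording, one standard additional analysis on data already being collected, and probably a less favourable stated power. No extra participants are required.

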Only participants whose mobility data are collected for at least 3 days will be included in analysis. If participants do not complete one of the study assessments (eg, Short Physical Performance Battery) or their data from the devices is not collected, their remaining data will still be included in analysis. Assuming missing data is at random, modern statistical techniques will be used to handle missing data and will be compared with a complete case approach.^41^

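### The check behind 55 participants does not reach its stated 95% power if 0.44 is a paired-difference effect size, and it leaves the sidedness and the effect-size definition undeclared

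*Protocol article*

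**What the plan says.** The sample size paragraph (protocol article, Recruitment and screening, after the Figure 1 caption) has two steps.

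- **Initial choice.** The authors explain that too little was known for a reliable power calculation before the start, and that "a convenience sample size of 55 was defined according to COnsensus-based Standards for selection of health Measurement Instruments guidelines".
- **Later check.** "The sample size was evaluated using data collected in 30 participants, with GPower V.3.1", "assuming an effect size of 0.44 for a change in mobility" between the off and on states. The outcome is described as "gait speed, shown to be improved by levodopa in lab studies". The remaining settings and the conclusion are given as: "repeated paired t-test, alpha of 0.05 and beta (power) of 0.95). This highlighted that our sample size of 55 participants was appropriate".

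The paragraph does not say whether the test is one- or two-sided, how the effect size is standardised, what sample size GPower returned, or what power 55 achieves.

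Under Data analysis, the article adds: "Only participants whose mobility data are collected for at least 3 days will be included in analysis".

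**The concern.** The paragraph prints enough inputs to be checked, and a reader will take it to mean that 55 participants give 95% power to detect an effect of 0.44. A bare alpha of 0.05 is conventionally read as two-sided. On that reading, and with 0.44 as a paired-difference effect size, the type II error at 55 is about twice the 5% implied.

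Walking speed is one of the primary outcomes listed under Seven-day remote monitoring period. A null or imprecise on/off comparison of gait speed would therefore be judged against a power that the printed inputs do not establish. The beta label adds to the confusion: taken literally, beta of 0.95 would be power of 5%.

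**Working it through.** **Inputs from the sample size paragraph.** n = 55; effect size 0.44; paired t-test; alpha 0.05; target power 0.95; GPower 3.1. Not given: sidedness and the definition of the effect size. Both are varied below.

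**Formula.** For a paired t-test with standardised mean difference dz (mean of the paired differences divided by their SD), df = n − 1 and the noncentrality is dz·√n. Power is the probability that a noncentral t exceeds the critical value (for a two-sided test, the small opposite tail is added).

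**Step 1. Try to reproduce 95% at 55, with dz = 0.44.** Noncentrality = 0.44 × √55 = 3.263, df = 54.

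| Test | Critical t | Power at 55 | Smallest n for 95% | dz detectable at 55 with 95% power |
|---|---|---|---|---|
| Two-sided 0.05 | 2.005 | 89.3% | 70 | 0.495 |
| One-sided 0.05 | 1.674 | 94.3% | 58 | 0.449 |

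The type II error is 10.7% two-sided and 5.7% one-sided, against 5%. The shortfall in participants is 70 − 55 = 15 or 58 − 55 = 3.

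**Step 2. Cross-check by the normal approximation**, n = ((z_alpha + z_power)/0.44)².

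- Two-sided: ((1.960 + 1.645)/0.44)² = 67.1, so 68.
- One-sided: ((1.645 + 1.645)/0.44)² = 55.9, so 56.

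The nearest route to 55 is therefore a one-sided test.

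**Step 3. Rounding of the effect size.** For dz from 0.435 to 0.4449, power at 55 is 88.7% to 90.0% two-sided and 93.8% to 94.7% one-sided. The required n is 68 to 71 two-sided and 57 to 59 one-sided. No dz that rounds to 0.44 reaches 95% at 55.

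**Step 4. The other reading of 0.44.** If 0.44 is the on/off difference divided by the between-person SD (taken as equal in both states), then dz = 0.44/√(2(1 − r)), where r is the within-person correlation. The document gives no r, so these values are assumptions:

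| r (assumed) | dz | Two-sided power at 55 |
|---|---|---|
| 0.4 | 0.402 | 83.3% |
| 0.5 | 0.440 | 89.3% |
| 0.61 | 0.498 | 95.2% |
| 0.7 | 0.568 | 98.5% |

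On this reading, 55 can fall short of 95% or exceed it.

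**Step 5. Fewer evaluable participants (illustration only).** The document gives no loss rate. If 50 of 55 met the 3-day rule, dz = 0.44 would give 86.2% two-sided or 92.3% one-sided.

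**Step 6. The label.** Power = 1 − beta, so power of 0.95 means beta = 0.05.

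**The case against.** The strongest reply is that the material shortfall depends on choices the paragraph never makes. It does not say the test is two-sided, and it cites a directional expectation from laboratory studies. One-sided, 55 falls short by only 0.7 percentage points, or 3 participants. It also does not say that 0.44 refers to paired differences; with a between-state effect size and a correlation of about 0.61, 55 meets 95% even two-sided. This stands. A reader might infer that the 95% claim is flatly false and 55 too small, but the document does not support that. What remains is that the printed inputs do not establish 95%. The directional remark describes the effect; it does not declare a one-sided test.

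A reader might also infer that this is the only justification for 55. It is not: the number came first, as a convenience sample set by measurement-instrument guidelines, and the power calculation was a later check.

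Nor does a formal decision hang on the test. The study is observational, and the Statistical analysis section plans descriptive statistics, functional data analysis, deep learning and non-linear time series analysis, without naming a paired on/off t-test. Power of 89% may well be adequate for such a study. This lowers the severity but does not make the figure right.

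Finally, the absence of a dropout allowance is not a finding in itself. The article condenses a fuller protocol, and any loss rate used here is an assumption.

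**Conclusion.** The point holds in limited form, with moderate severity.

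- With 0.44 as the standardised mean of paired differences, 55 participants give 89.3% power two-sided or 94.3% one-sided, not 95%. Only the undeclared one-sided test comes close.
- With 0.44 as a between-state standardised difference, the power cannot be determined, because the within-person correlation is not stated.
- The beta label is wrong on every reading.

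The results rest on the paired t-test and alpha as printed, and the correlations are assumed. None of this shows that 55 is the wrong number of participants. It shows that the power attached to 55 is incompletely specified and, on the conventional two-sided reading with a paired-difference effect size, overstated by about 6 percentage points (95 − 89.3 = 5.7).

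**What to change.** Keep 55 and rewrite the check.

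1. Declare whether the test is one- or two-sided, with a justification if it is one-sided.
2. Define the 0.44: standardised by the SD of the paired differences, or by the between-person SD. In the second case, give the within-person correlation used and its source.
3. Replace the 95% with the power that 55 achieves under those declarations. On paired differences this is 89% if two-sided, with an effect of about 0.50 detectable at 95% power, or 94% if one-sided. On the between-state definition, it is the figure that follows from the declared correlation.
4. Correct the label so that 0.95 is called power, wherever that target is still mentioned.
5. Optionally, add the power at a lower evaluable number in view of the 3-day rule, marked as an assumption: for example, 50 evaluable gives 86% two-sided or 92% one-sided on paired differences.

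The authors must supply items 1 and 2; the document does not allow a reviewer to fill them in. The cost is wording only, with no extra participants and no change of design. The downside is that, on paired differences, the stated power becomes less favourable.
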